**Methods:**

We will conduct a randomized controlled trial among 398 mothers enrolled in a Dutch home visiting program targeting families at risk for child maltreatment. Mothers in the experimental group will receive the manualized components in two consecutive home visits, while mothers in the control group will receive regular home visits (care as usual). Mothers will fill out questionnaires at four time points: before and after each of the two home visits. Outcome variables include the four targeted risk factors parental self-efficacy, perceived stress, parental anger, and (recognition of) post-traumatic stress symptoms, as well as parenting practices (e.g., rejection and affection), and risk for child maltreatment.

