## Methods/design

### Design

We will conduct a randomized controlled trial in the context of an existing Dutch home visiting program aimed at the prevention of child maltreatment (Supportive Parenting, in Dutch “*Stevig Ouderschap*” [54]). Mothers will be randomly assigned to receive either two consecutive home visits that include the additional manualized components (i.e., manualized home visiting), or to receive standard home visits (i.e., care as usual) with a 1:1 allocation using a computerized random number generator.

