#### Parental anger

Mothers report on parental anger on the ‘expression’-subscale of the Parent Anger Scale (PAS [70]). This questionnaire assesses anger experience in the parent-child context. The PAS expression subscale has high internal consistency (α = .95) and correlates to other measures of negative affect and discipline strategies [75]. Mothers rate 11 items such as ‘I get so angry with my child, that I scream or yell at my child’ on a seven-point scale ranging from 0 (*never*) to 6 (*several times a day*).

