#### Risk for child maltreatment

Mothers report on their risk for child maltreatment on the Instrument for early identification of Parents At Risk for child Abuse and Neglect (IPARAN [54]). This is the same questionnaire that youth health care centers use to screen families for the Supportive Parenting program. Mothers rate nine items, such as ‘I can get so angry that I lose control’ on a scale ranging from 1 (*always*) to 4 (*never*) and answer seven yes/no items, such as ‘I feel that my parents/carers hit me too much as a child.’ The items differ in their scoring and answers correspond with scores of either 0, 0.1, 0.2, 0.3, 0.5, or 1 (for more details, see [76]). The IPARAN has shown to adequately predict future reports of child maltreatment [76]. Youth care centers use a simplified rating system where answers are scored as 0, 0.5, 1, 1.5, or 2. Families where at least one parent scores ≥3 are offered the Supportive Parenting program.

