### Sample size calculation

As we will compare two active conditions, we expect to find relatively small effects. More specifically, we expect moderate effects on the targeted risk factors (i.e., our more proximal outcome measure) and a small effect on mothers’ risk for child maltreatment (i.e., our more distal outcome measure). Previous additive studies (i.e., studies in which effects of an intervention are compared to effects of the same intervention with one or more additional components) also demonstrated small to moderate average effect sizes for interventions with added components [77]. Our sample of *N =* 398, with two groups and one-sided tests at α = .05 provide us with a power (1 – β) of .80 to detect effects of *d* = .25 [78]. Following the guidelines of Fritz and MacKinnon [79], our sample size will also allow for sufficient power to detect mediation effects when using mediation analyses based on bootstrapping.

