### Analyses

Prior to analyzing the data, missing data will be handled with multiple imputation. To test whether adding manualized components ameliorates four risk factors (i.e., low parental self-efficacy, high levels of perceived stress, parental anger, and post-traumatic stress symptoms), improves parenting practices, and reduces risk for child maltreatment, we will conduct multivariate analyses of covariance (MANCOVA) and an analysis of covariance (ANCOVA) respectively, with baseline scores (T1) as the covariates, with data of T2, T3, and T4 for the risk factors and data of T4 for parenting practices and risk for child maltreatment as dependent variables.

To test whether amelioration of the targeted risk factors by the added components explains (i.e., mediates) reduced risk for child maltreatment we will conduct a mediation analysis using the PROCESS Macro in SPSS [80]. This macro computes 95% confidence intervals of the indirect effects based on 1000 bootstrap samples. Intervals that do not include 0 indicate a mediation effect.

To test who benefits most from the manualized components we will test whether condition × child, maternal, or family characteristic interaction effects predict ameliorated risk factors and reduced risk for child maltreatment. Putative moderators include mothers’ baseline levels of each of the four risk factors (maternal characteristics), children’s temperament (child characteristic), and the number of life events in the past year and during the study (family characteristic).

We will conduct interim descriptive analyses for our progress annual reports for the study funder. However, no interim analyses that answer the research questions of this study will be conducted. The full protocol, anonymized dataset, and the statistical code that will be used in this study will be available upon motivated request after publication of the results in a peer-reviewed paper.

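### The indirect effect through parental anger is partly built in, because the IPARAN outcome contains an anger item that overlaps with the anger mediator

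*Protocol article*

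**What the plan says.** Aim 3 asks whether reduced maltreatment risk is explained by improvement in the four targeted risk factors. For this, the Analyses section states: "we will conduct a mediation analysis using the PROCESS Macro in SPSS". It uses 95% bootstrap intervals from 1000 resamples and this decision rule: "Intervals that do not include 0 indicate a mediation effect".

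The anger mediator is the 11-item expression subscale of the Parent Anger Scale. The Parental anger section illustrates it with "I get so angry with my child, that I scream or yell at my child". The outcome is the IPARAN, with nine rated and seven yes/no items. The Risk for child maltreatment section illustrates its rated items with "I can get so angry that I lose control" and says that items differ in their scoring, with values from 0 to 1.

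On power, the Sample size calculation section gives "one-sided tests at α = .05 provide us with a power (1 – β) of .80" for d = .25 at N = 398. It then says of mediation that "our sample size will also allow for sufficient power to detect mediation effects when using mediation analyses based on bootstrapping", with no path sizes. The same section expects moderate effects on the risk factors and a small effect on maltreatment risk.

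**The concern.** A mediation claim needs the mediator and the outcome to be different things. Here both ask how the mother's anger comes out. The experimental arm is taught ways to calm down when angry, so if that works, the IPARAN anger item should improve along with the anger scale. The total then falls even if no other element of maltreatment risk changes. The product of the two paths is non-zero because of how the outcome is scored, and the decision rule reads this as mediation.

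The Discussion would take a positive mediation result as support for the theory that these risk factors contribute to maltreatment. For anger, that support would be partly circular. The Limitations section does not mention the overlap.

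The power sentence is a smaller matter. The trial is sized with a one-sided test, mediation is judged by a two-sided interval, and no path sizes show what sufficient means.

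**Working it through.** **1. The plan's own figure.** Inputs: "randomized controlled trial among 398 mothers", "with a 1:1 allocation using a computerized random number generator" (199 per arm), d = .25, one-sided α = .05, power .80.
- Normal approximation: n per arm = 2(1.645 + 0.842)² / .25² = 197.9, so 198 per arm (396 in total).
- One-sided two-sample t-test: 199 per arm, 398 in total, with power .80. The stated N reproduces exactly.

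**2. How far item overlap alone can carry the decision rule.** The documents give neither the item weights in use nor the correlations, so this is an illustration. Assumptions:
- m equally weighted, mutually uncorrelated IPARAN items
- exactly one anger item
- all other items unrelated to the anger scale
- correlation k between the anger scale and the anger item, from .5 to .9
- no baseline adjustment

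The correlation of the anger scale with the total is then r = k/√m. The mediator-outcome path has z = r√398 / √(1 − r²) and power Φ(z − 1.96). The chance that the interval excludes 0 is approximated by the product of the powers of the two paths.

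Treatment-to-anger path: z = d√(199/2). This is 4.99 at d = .5 (power .999) and 2.49 at d = .25 (power .70).

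| Items counted | k | r | z | Mediator-outcome power | Product, d = .5 | Product, d = .25 |
|---|---|---|---|---|---|---|
| 9 | .5 | .167 | 3.37 | .92 | .92 | .65 |
| 9 | .9 | .300 | 6.27 | 1.00 | 1.00 | .70 |
| 16 | .5 | .125 | 2.51 | .71 | .71 | .50 |
| 16 | .9 | .225 | 4.61 | 1.00 | .99 | .70 |

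Simulation under the same assumptions gave 91–100% (nine items) and 70–99% (16 items) at d = .5, and 49–70% at d = .25. In every row the components change nothing in the IPARAN except its anger item.

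**3. Power of the mediation test itself.** A 95% interval corresponds to two-sided α = .05. At d = .25 and 199 per arm, power for the treatment-to-mediator path falls from .80 to Φ(2.49 − 1.96) = .70, which caps the indirect effect at about that value. Results with one mediator, no covariates, 1000 percentile-bootstrap resamples and 400 simulated trials (mediator-outcome path b is assumed, as the protocol gives none):

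| d on mediator | b = .14 | b = .20 | b = .25 |
|---|---|---|---|
| .25 | .55 | .66 | .71 |
| .5 | .82 | .98 | 1.00 |

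Values of b from .25 to .50 at d = .25 gave .71 to .73, which is the cap within simulation error.

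Adjusting for T1 raises the power of the treatment-to-mediator path at d = .25 to .74, .82 or .94 for assumed baseline correlations of .3, .5 or .7 (effective d = .25/√(1 − ρ²)).

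**The case against.** The strongest reply on overlap is that the documents show only one anger item among 16. It is worded generally, whereas the mediator scale concerns anger at the child. Item weights are unequal, so no figure in the illustration is an estimate for this trial. It can also be said that losing control in anger belongs to maltreatment risk, so a change there is a real change in the score. All of this is fair. It limits the size of the claim and confines it to one mediator, but it does not remove the overlap. Counting all 16 items lowers the illustrated rate at d = .5 to about 70% at its lowest, not to a negligible level. A real change in the anger item is still not evidence that anger drives the rest of maltreatment risk.

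On power, a reader might infer that N = 398 is too small for the mediation analysis. The documents do not support that. The d = .25 is the detectable difference of the group comparison, while the protocol expects moderate effects on the mediators. With d = .5 taken as moderate, a single-mediator model is adequate, and T1 adjustment helps further. There is one qualification. With four parallel mediators correlated at .4, d = .5 and b = .14, power was .66 in a simulation of only 100 trials; it was .99 at b = .26.

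A reader might also infer that the mediators will be measured at the same time as the outcome. The mediation paragraph names no wave, but Table 1 shows the risk factors at T2 and T3, before the T4 IPARAN. The choice of wave is a detail that an article may leave to the full plan.

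**Conclusion.** The overlap stands. The anger mediator and the IPARAN share anger-expression content by the protocol's own example items, and the stated decision rule would count that shared content as mediation. The direction is clear: it favours finding mediation by anger. The size cannot be computed from the documents. The illustrated range of about 70–100% at d = .5 (about 50–70% at d = .25) rests on equal weights, otherwise unrelated items and k of .5 to .9.

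It would go too far to say that Aim 3 as a whole is compromised. Self-efficacy, perceived stress and post-traumatic stress symptoms are not shown to share items with the outcome.

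Secondarily, the statement of sufficient mediation power is incomplete rather than wrong. It depends on the expected moderate effects on the mediators (or on baseline adjustment) and does not hold at d = .25 unadjusted, where power is at most about .70.

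**What to change.** 1. For the anger mediator, also run the mediation analysis with the IPARAN scored without its anger item(s), alongside the full validated score. Claim mediation by anger only if the result holds in both. Name the removed item(s) before the outcome data are analysed.
2. Add the overlap to the Limitations.
3. In the Sample size calculation section, give the treatment-to-mediator and mediator-outcome effects behind the mediation power claim. Say that it rests on the expected moderate effects on the risk factors, and note that the 95% interval without baseline adjustment gives at most about .70 at d = .25.

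The cost is wording and one extra analysis, with no new data; the protocol reports recruitment as ongoing. The downside is that the reduced IPARAN is not the validated total, which is why the full score stays beside it.

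### The mediation verdict rests on an interval from only 1000 bootstrap samples, so a result near the boundary can change with the random seed; this is uncommon and cheap to reduce.

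*Protocol article*

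**What the plan says.** The Analyses section of the protocol article names the tool for aim 3: "we will conduct a mediation analysis using the PROCESS Macro in SPSS". It fixes the number of resamples, "This macro computes 95% confidence intervals of the indirect effects based on 1000 bootstrap samples", and then the decision rule: "Intervals that do not include 0 indicate a mediation effect". The number and the rule are therefore both stated in the article and not left to another document. The type of bootstrap interval is not named. The candidate mediators are the four targeted risk factors, and the outcome is risk for child maltreatment. The Sample size calculation section calls the power for mediation sufficient, but gives no figure and no path sizes.

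**The concern.** A bootstrap limit is itself an estimate from random draws. At the 2.5% point, 1000 draws leave about 25 in the tail, so the limit moves a little from run to run. That does no harm when the limit is reported as a number well away from 0. It matters when the limit becomes a binary verdict and lies close to 0, because a rerun of the same data can then reverse the answer. Mediation is one of the four study aims, and the Discussion section would take a positive answer as support for the theory of change. Noise of this kind is not sampling uncertainty: it comes from the computing and can be reduced without any further data.

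**Working it through.** **Inputs from the article.** B = 1000 resamples, 95% intervals, and the rule that an interval excluding 0 means mediation (Analyses); N = 398 (abstract and Participants); allocation 1:1 (Design), so 199 per arm.

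**Assumptions, not in the article.** An equal-tailed percentile interval. For the frequency calculation, a condition-to-mediator effect of d = 0 to 0.50 and a mediator-to-outcome path of b = 0.14 to 0.30.

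**The plan's own figure.** The Sample size calculation section says "one-sided tests at α = .05 provide us with a power (1 – β) of .80" "to detect effects of *d* = .25". The normal formula gives n per arm = 2 × (1.645 + 0.842)² / 0.25² ≈ 198, or 396 in total. Power at 199 per arm is 0.802 (normal) or 0.801 (t). N = 398 reproduces. It says nothing about bootstrap precision and is used below only as the sample size.

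**Step 1: Monte Carlo error of the tail.** SE = √(0.025 × 0.975 / B). The 95% band is 0.025 ± 1.96 × SE.

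| B | SE of the 2.5% tail | Seed-sensitive tail shares | SE of the limit, in standard errors of the indirect effect |
|---|---|---|---|
| 1000 | 0.49 points | about 1.5% to 3.5% | 0.084 |
| 5000 | 0.22 points | about 2.1% to 2.9% | 0.038 |
| 10,000 | 0.16 points | about 2.2% to 2.8% | 0.027 |

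**Step 2: chance of the wrong verdict, given a near-boundary result.** Let p be the share of resamples beyond 0 that unlimited resampling would give. The number beyond 0 in B resamples is binomial (B, p), and 0 is excluded when that number is small enough. At B = 1000 the answer depends on whether a count of exactly 25 excludes 0, so both conventions are shown. For 5000 and 10,000 the figures use the convention that it does not; the other convention differs little.

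| p | Correct verdict | Wrong at 1000 | Wrong at 5000 | Wrong at 10,000 |
|---|---|---|---|---|
| 0.020 | excludes 0 | 11% to 15% | 0.8% | 0.03% |
| 0.022 | excludes 0 | 22% to 29% | 8% | 2% |
| 0.030 | includes 0 | 15% to 20% | 1.5% | 0.1% |

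Away from the boundary the verdict is stable even at 1000. Counting 25 as excluding 0, mediation is declared in 99.4% of runs at p = 0.015 and in 0.7% at p = 0.040.

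**Step 3: how often a trial lands there.** If q is the chance that one run declares mediation, two seeds disagree with probability 2q(1 − q). Averaging this over simulated trials of 398 mothers, at B = 1000 and per indirect effect, a normal approximation to the path estimates gives:

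- d = 0.50, b = 0.30: 0.06%
- d = 0.50, b = 0.14: 2.5%
- d = 0.25, b = 0.30: 3.3%
- d = 0.25, b = 0.14: 4.8%
- d = 0, b = 0.30: 1.0%

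A bootstrap simulation of 300 data sets with a = 0.25 SD and b = 0.30 gives 3.0% at B = 1000, 1.5% at 5000 and 1.0% at 10,000. Of the 2.0-point reduction (3.0 − 1.0), 1.5 points are already reached at 5000. A further simulation gives 0.03% to 4.6% at 1000 and at most about 1.5% at 10,000.

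**The case against.** The strongest reply is that this is a software setting, not an error. Nothing in the Analyses section is false or contradictory. Aim 3 is a question of mechanism, and the primary outcomes are tested by MANCOVA without any bootstrap. A tail share between 1.5% and 3.5% is borderline evidence however many draws are taken, and at exactly 2.5% the verdict is still close to a coin toss with 10,000 samples. All of this stands, and it keeps the point minor. It does not remove the point, because the article itself fixes the number 1000 and ties a yes/no verdict to it.

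Three stronger readings are tempting and are not supported:

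- A reader might infer that small planned effects will often put indirect effects near the boundary. The Sample size calculation section expects moderate effects on the targeted risk factors, which are the mediators, and a small effect only on maltreatment risk. Nearness to the boundary also depends on the estimate relative to its standard error, not on effect size alone.
- A reader might take 11% to 29% as the error rate of the mediation analysis. Those figures hold only once the tail share is already close to 2.5%.
- A reader might count the absence of a seed as a defect. An article may leave the seed to the code, and this one says that the code will be available on request after publication.

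**Conclusion.** The point holds as a minor, avoidable weakness. With 1000 resamples the yes/no answer for an indirect effect is seed-dependent inside a narrow band of tail shares, and the band shrinks markedly with more resamples. The band and the conditional error rates depend only on B and on a percentile interval. The overall frequency, roughly 0.03% to 5% of trials per indirect effect, depends also on the assumed paths, for which the article gives no values. With four candidate mediators there are several chances for it to arise, but most verdicts would be the same under any seed.

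**What to change.** In the Analyses section, replace 1000 with a larger number of bootstrap samples, such as 10,000, for every indirect effect; 5000 already gives most of the gain. Recording the seed is good practice alongside this. The cost is one number in the text and a little computing time, with no change to design, data or sample. The article reports that data collection is ongoing and that no interim analysis will address the research questions, so at that stage the change can be made before any mediation result is known.

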## Discussion

Given the serious consequences of child maltreatment, and the typically modest effects of frequently used home visiting programs, it is important to know how programs can be improved to support families by reducing their risk for child maltreatment. This study strives to guide efforts to increase the effects of Supportive Parenting in particular, and the effects of child maltreatment prevention programs in general, by studying whether adding components that target compromised feelings of parental self-efficacy, high levels of perceived stress, parental anger, and post-traumatic stress symptoms, contribute to program effectiveness.

Scholars often seem divided in arguing for either manualized or flexible treatments (for an overview, see [81]). In this study, we bridge both approaches by adding a select set of manualized components while maintaining a level of flexibility. Our study sheds light on whether borrowing some of the advantages of either approach – manualized components to target key risk factors for child maltreatment and the flexibility to adjust program content according to clinical experience – yields larger effects than a more flexible approach.

Research on the effects of a limited set of program components helps us unravel the effects of parenting programs, by identifying the merit of discrete program components, above and beyond other components and common elements [82]. Knowledge on the effectiveness of program components can therefore refine theories about mechanisms of change that underlie program effectiveness.

Understanding whether any effects of the four manualized components on reduced risk for child maltreatment are mediated by amelioration in the four targeted risk factors, improves our understanding of the role of these risk factors in occurrences of child maltreatment. If amelioration of one or more of the targeted risk factors indeed explains a stronger reduction in the risk for child maltreatment yielded by manualized home visitation, this strengthens our theory that these risk factors indeed contribute to risk for child maltreatment [83].

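### The mediation rule cannot separate mediation from confounding between risk factor and maltreatment risk, yet a positive result is to be read as support for a contributory role

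*Protocol article*

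**What the plan says.** Aim 3 asks whether any effect of the components on maltreatment risk is mediated by improvement in the four targeted risk factors. The Analyses section assigns this to the PROCESS macro: "This macro computes 95% confidence intervals of the indirect effects based on 1000 bootstrap samples". The decision rule follows at once: "Intervals that do not include 0 indicate a mediation effect". No further condition is attached. T1 scores are named as covariates for the MANCOVA and ANCOVA; the mediation paragraph does not mention them.

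The Discussion says what a positive finding would mean. If improvement in a risk factor explains a stronger fall in maltreatment risk, "this strengthens our theory that these risk factors indeed contribute to risk for child maltreatment". The Limitations section notes that effects cannot be attributed to single components. It does not mention confounding between mediator and outcome.

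Under Measures, all four risk factors and IPARAN are maternal self-reports, and Table 1 schedules all of them at T1 and T4.

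**The concern.** An indirect effect is the product of two slopes: condition to risk factor (a) and risk factor to IPARAN given condition (b). Randomisation protects a but not b. The bootstrap measures sampling error in the product and says nothing about why risk factor and IPARAN go together.

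The article itself points to possible shared causes. IPARAN includes a yes/no item on having been hit too much in childhood, which no change in a current risk factor can alter, while the Background links traumatic experience to post-traumatic stress symptoms. The anger scale and IPARAN both ask about anger getting out of hand. One reporter supplies every score.

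Aim 3 is the trial's test of its theory of change. One package of components may move several risk factors at once, so the analysis has to tell factors that matter from factors that merely move. If b is partly non-causal, the stated rule cannot do that.

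**Working it through.** **Inputs from the article.** N = 398, allocated 1:1, so 199 per arm. The sample size rests on d = .25 and power .80, "with two groups and one-sided tests at α = .05". For the mediators, "we expect moderate effects on the targeted risk factors". The mediation interval is a 95% interval from 1000 bootstrap samples.

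**Assumptions, because the documents give no figure.** A moderate effect is taken as d = .5, with .25 as the lower case. The non-causal within-arm correlation r runs from 0 upwards. T1-T4 stability is .6. The true effect of mediator on outcome is zero. Mediators are taken one at a time.

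**Step 1: the plan's own figure.** n per arm = 2(1.645 + 0.842)²/.25² = 197.8, so 198 per arm, or 396. By the t-test, power is .799 at 198 per arm and .801 at 199, so 398 reproduces.

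**Step 2: the rule without T1 terms.** The interval excludes 0 roughly when both slopes are significant at two-sided 5%.

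- Slope a: the noncentrality is d√(199/2). Power is .701 at d = .25 and .999 at d = .5.
- Slope b: the noncentrality is r√395/√(1 − r²), which is 2.00, 4.06 and 6.25 at r = .1, .2 and .3. Power is .513, .982 and 1.000. At r = 0 it is .05.

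The product of the two powers, beside a simulation of the stated bootstrap rule (400 trials per cell):

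| r | d = .25: product | d = .25: simulated | d = .5: product | d = .5: simulated |
|---|---|---|---|---|
| 0 | 4% | 3% | 5% | 4% |
| .1 | 36% | 33% | 51% | 55% |
| .2 | 69% | 69% | 98% | 98% |
| .3 | 70% | 75% | 100% | 100% |

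A separate simulation gave 34%, 68% and 70% at d = .25 and 50%, 97% and 100% at d = .5 for r = .1, .2 and .3. At d = .25, among simulated trials with a significant effect on the mediator, mediation was declared in 46% at r = .1 and 97-99% from r = .2. With d = 0 the rate stays at about 5% or below.

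**Step 3: T1 mediator and T1 IPARAN as covariates.** The result depends on how scores persist.

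- *Stable trait plus occasion-specific state.* Each T1 score correlates .6 with its own T4 score, and every mediator-outcome pair correlates r. At r = .2 the T4 residual covariance is .2 − .1667 = .0333 and the residual variance is 1 − .3667 = .6333, so the partial correlation is .0333/.6333 = .053. At r = .3 and .4 it is .085 and .125. The noncentrality of b (now with √393) is 1.04, 1.68 and 2.50, with power .18, .39 and .70. Slope a has power of about .88-.89 at d = .25 and 1.00 at d = .5. False mediation is then 16%, 34% and 63% at d = .25, and 18%, 39% and 70% at d = .5. Simulations gave 15-17%, 35-38% and about 63-65% at d = .25, and 18% and 40% at d = .5 for r = .2 and .3. At r = .5 the simulated rates are 84% and 96%.
- *Autoregressive process with no new shared causes.* The T1 scores carry all of the shared cause. The rate is 4-5% with T1 covariates, and 21-58% (d = .25) or 29-82% (d = .5) without them.

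**Step 4: change in IPARAN as outcome, T1 mediator as covariate (trait-state model, d = .25).** The rate is about 4-5% if T4 states are uncorrelated, about 17% if they correlate .1, and 52-55% if they correlate .2. No handling of baseline removes an influence that mediator and outcome share at T4.

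**Step 5: requiring a total effect on IPARAN first.** If the components reach IPARAN by no route at all, the rate falls to about 3-5%. If they reduce risk by a route other than the mediator in question, it stays at about 62-93%.

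**The case against.** The best case for the plan has four parts.

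First, the aim concerns explaining an effect on maltreatment risk, and the Discussion's conclusion presupposes a stronger reduction under the manualised visits. In a trial with no such effect that premise is mostly unmet. This stands in part: the high rates in step 2 would fall to 3-5% under such a gate. But the Analyses section writes no gate, and a gate does not help where another risk factor carries the effect, which is the case aim 3 has to resolve.

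Second, the article condenses a fuller protocol, which may add baseline covariates. The references to amelioration and reduced risk hint at change or baseline adjustment. This also stands in part. Silence on covariates is not itself the fault; the unqualified rule and the reading given to it are. Adjustment helps by an amount the documents do not let us determine.

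Third, to strengthen a theory is not to prove it, and a mediation pattern that could have failed is some evidence. True, but such evidence is weak if the rule fires about as often when the factor plays no role.

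Fourth, the rates rest on assumed correlations. That is correct. A reader might infer that any component effect on a risk factor will usually be declared mediation, whatever the factor's role. The documents do not support that: they give no within-arm correlation, the rate is nominal at r = 0, and false declarations become the usual result at both effect sizes only from about r = .2. Nor do they support the inference that ordinary T1 adjustment must fail, since under the autoregressive model it works.

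**Conclusion.** The concern holds in limited form. The rule tests whether condition moves the risk factor and whether that factor is associated with IPARAN within arms. It cannot tell mediation from mediator-outcome confounding, and the Discussion draws a contributory conclusion without stating the assumption that this needs.

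The size is conditional. Without T1 terms, false mediation is 3-4% at r = 0, 33-55% at r = .1, and from r = .2 about 70% at d = .25 and 97-100% at d = .5. With T1 covariates it runs from about 5% to 65-70% for r up to .4. These figures assume zero mediator effect, stability of .6, one mediator at a time and no total-effect gate. The trial's tests of aims 1 and 2 are unaffected.

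**What to change.** In the Analyses section, state that the T1 scores of the mediator and of IPARAN are covariates in both PROCESS equations, with the T4-T1 change in IPARAN as a sensitivity model. Replace the rule with wording to this effect: an interval excluding 0 is reported as an indirect effect, which is causal only if there is no unmeasured mediator-outcome confounding.

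For each mediator, report the residual mediator-outcome correlation at which the indirect effect becomes 0. Use it as a description, not as a pass/fail threshold. In the change model, power for a true mediator effect of .3 is about 79-80% at d = .25 and 90-91% at d = .5. Requiring the interval to survive an assumed residual correlation of .1 would cut this to about 22-26%, and one of .2 to below 1%.

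In the Discussion, make the claim about strengthening the theory conditional on that assumption and on the reported robustness. Add mediator-outcome confounding to the Limitations.

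The cost is a few sentences, slightly more analysis and a more cautious mediation claim. No new data are needed, because Table 1 already schedules every score at T1 and T4. Recruitment is described as ongoing and no interim analysis of the research questions is planned, so the change can be made before those results are known.
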